Our project baseline during April to December 2012 in Bajhang, Dailekh and Kanchanpur districts of Mid and Far Western Development region in collaboration with GoN and financial and technical support form WHO Geneva reported first ANC coverage of 88% while 4^th^ and more ANC visit of 65% in average. Only the half of the respondents (52%) knew about danger signs during pregnancy and delivery and 19% of them had faced complications during last delivery.

Our survey reported, 45% of births were assisted by SBA/THW which ranges from a high of (64%) in Kanchanpur and a low of (33%) in Bajhang. Which is low as compared to MDG target to scale up SBA coverage to 60% by 2015 [13]. This suggests additional efforts are required in scaling up skilled birth attendants in Nepal. This requires innovative intervention that uniquely address identified barriers in receiving care. Distance to reach health facility, lack of transportation means to reach the health facility, lack of information about the availability of services in health facilities were the identified barriers.

Amidst of possibilities and challenges in SBA service scale up, Nepal Public Health Foundation (NPHF) [24] has taken initiative and has been conducting a study on “Overcoming Barriers to Scaling Skilled Birth Attendants Utilization in Improving Maternal, Newborn and Child health in Nepal” as a three-year implementation research project with support from WHO-HQ, Geneva. The overall aim of the implementation research is to increase SBA service utilization by identifying the barriers related to service users and health systems regarding the utilization of skilled birth attendants and implementing a package of interventions to address these barriers.

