### Primary output

Utilization of SBA services by the women for childbirth.

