### Secondary output

Ante-natal care visits for 4 times by pregnant women

Post natal care visits of mothers and babies

Availability of transport to the women to visit health institutions for childbirth

Functional operation of emergency fund

Security of SBA

Family support to the women for childbirth at health institution

Women friendly health facility environment

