### Analysis strategies

Data will be double entered into EpiData 3.1, validated using Epi Info data compare, and will be transferred to SPSS 16 for analysis. The findings from quantitative tool will be presented in tabular and graphical forms. To control for more than one confounding variable multivariate logistic regression model will be applied. For statistical inference of the result, a confidence level of 95% is set. For the analysis process of qualitative data collected form FGD, the transcription of taped FGD session will be typed and reviewed thoroughly then translated in English language by field coordinators. The content of transcription will then be labeled as per the domain of analysis.

Missing data will be characterized in terms of the degree and patterns of missing data. For imputation of missing value of categorical variables, the frequency distribution will be used as the basis for randomly generating a value for each observation lacking a response. For example, if education was measured in three categories -- “less than high school” (25% of complete data cases), “completed high school” (40%), or “more than high school” (35%) -- then for each observation with education missing, a random number between 0 and 1 will be drawn from a uniform distribution and the missing value replaced with “less than high school” if the random number is less than or equal to 0.25, “completed high school” if the number is greater than 0.25 but less than or equal to 0.65, or “more than high school” if greater than 0.65. For imputation of numerical variable regression method is used.

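### Regression imputation of numerical variables reads as single imputation, which would understate the standard error of outputs analysed on the filled values

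*Protocol article*

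**What the plan says.** The Analysis strategies section of the protocol article opens its treatment of missing data with "Missing data will be characterized in terms of the degree and patterns of missing data". It then gives two filling rules.

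- Categorical variables: "the frequency distribution will be used as the basis for randomly generating a value for each observation lacking a response". The worked example, on education, draws one uniform random number per incomplete record and puts one category in its place.
- Numerical variables: "For imputation of numerical variable regression method is used". Nothing more is said.

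Repeated imputation, pooling and variance correction are not mentioned. The same section sets a 95% confidence level and names one model: "To control for more than one confounding variable multivariate logistic regression model will be applied". Neither rule says whether outputs are to be filled, and neither exempts them.

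The primary output is "Utilization of SBA services by the women for childbirth", a yes/no item. The secondary outputs include "Ante-natal care visits for 4 times by pregnant women". The baseline results in the Background give "first ANC coverage of 88% while 4^th^ and more ANC visit of 65% in average". The article does not say whether antenatal visits are stored as a number or a category, and it gives no expected rate of missing data.

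**The concern.** The section commits to imputation and describes the categorical half in enough detail to show that each gap is filled once. The numerical rule follows directly, with no sign that it works differently. If the result is one completed data set, the analysis treats filled values as information that was collected. Standard errors of quantities built on those values are then too small, and the stated 95% level is not met for them.

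A second, conditional worry is the four-visit output, which also appears in the first secondary objective. If visits are held as a count, and a missing count is replaced by a bare regression prediction, the predictions bunch near the mean. The share of filled women at or above four need not then match that of comparable observed women. The arm-level rate would move with the amount of missing data, and unequal missingness between arms could produce a spurious difference.

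**Working it through.** The plan states no figure here, so there is none to reproduce. The checks below rest on assumed inputs.

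**1. Inputs.** From the article: 88% with a first antenatal visit, 65% with four or more, 95% confidence level. Assumed: fraction missing *m* of 5%, 10% or 20%; share of variance explained by the imputation regression *R²* of 0.05 to 0.30; values missing completely at random; independent women (no clustering).

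**2. Standard error of a mean, one bare prediction per gap.** In units of the outcome variance over *n*:
- variance reported from the completed data: (1 − m) + m·R²
- true variance of the estimate: (1 − R²)/(1 − m) + R²
- reported/true standard error: √[(1 − m) + m·R²] / √[(1 − R²)/(1 − m) + R²]

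| m | R² = 0.05 | R² = 0.30 |
|---|---|---|
| 5% | √0.9525/√1.0500 = 0.95 | √0.9650/√1.0368 = 0.96 |
| 10% | √0.9050/√1.1056 = 0.90 | √0.9300/√1.0778 = 0.93 |
| 20% | √0.8100/√1.2375 = 0.81 | √0.8600/√1.1750 = 0.86 |

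**3. Simulation of the same quantity.** 1,000 runs, 500 women per arm, no arm effect, no clustering, R² of 0.05 and 0.20. The entries are reported/empirical standard error of the mean difference, with 95% interval coverage in brackets.

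| m | bare prediction | prediction plus one random residual |
|---|---|---|
| 5% | 0.95–0.97 (94%) | 0.95–0.97 (93–94%) |
| 10% | 0.91–0.93 (93–94%) | 0.92–0.93 (93%) |
| 20% | 0.79–0.83 (88–89%) | 0.82–0.85 (89–90%) |

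Complete cases, which are valid under this missingness, gave ratios of 0.98 to 1.02 and coverage of about 95%. The ratios carry simulation noise: with nothing missing they ran from 0.97 to 1.03. Adding a residual does not remove the understatement, because the cause is filling once and not pooling.

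**4. Limits of steps 2 and 3.** Both concern a mean. The ratio for a yes/no indicator cut from a filled count was not calculated; with bare predictions its main error may be a shift in level (step 5). In a cluster analysis, between-VDC variance adds to both the reported and the true variance, so the ratio moves towards 1. That was not quantified.

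**5. Four-visit rate, if a count is filled by bare prediction.** The two baseline percentages fix only a minimum mean. Of all women, 88% − 65% = 23% have one to three visits, so the mean is at least 0.23 × 1 + 0.65 × 4 = 2.83. There is no upper limit short of the largest count. The shift is *m* × (share of filled women at four or more − 0.65).
- Three distributions matching 88% and 65%, with means 3.11, 3.43 and 3.81: filled share 0–44% unrounded and 11–74% rounded. At m = 10% the shift runs from 0.10 × (0 − 0.65) = −6.5 points to 0.10 × (0.74 − 0.65) = +0.9 points.
- Two others matching the same percentages, with means 4.18 and 4.44: filled share 55–63% and 62–77% unrounded. At m = 10% the shift runs from 0.10 × (0.55 − 0.65) = −1.0 to 0.10 × (0.77 − 0.65) = +1.2 points.
- The simulated count of step 3 (rounded normal, mean 4.3, SD 2.2) has 64% at four or more. With rounded bare predictions this rose to 66–67% at 10% missing and 67–70% at 20%. It does not reproduce the 88%: (0.5 − 4.3)/2.2 = −1.73, so about 96% have at least one visit.
- With a residual added, the simulated share stayed at 64%.

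A shift is therefore possible, but its sign depends on a count distribution that the article does not give.

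**The case against.** The strongest reply is that the article says only that a regression method is used. It does not exclude an added residual or several imputations, and a condensed article may leave predictors, residual term and number of imputations to a fuller document. That stands as far as it goes: single imputation is an inference. It is still the natural one, since the adjoining rule is spelled out as a single fill and nothing in the section points to pooling. For the same reason, the absence of arm, district or VDC from the described regression is not a fault in itself.

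A reader might go further and infer that the plan prescribes a bare prediction that misclassifies women on the four-visit output. The documents do not support this. They do not say that the residual is left out, that visits are stored as a count, or that outputs are filled at all; the only worked example is education, a background variable. If the item is stored as yes/no, the numerical rule never reaches it. Nor do 88% and 65% place the mean below four.

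It is also fair to say that no listed output is described as a numerical mean, that the primary output is categorical, and that filling a covariate in the logistic model probably changes the standard error of the arm comparison little (this was not simulated). These points limit the reach of the problem but do not make the stated method sound where it applies.

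**Conclusion.** The point holds in limited form. As written, the numerical rule appears to be single imputation analysed as observed. Where the filled variable is itself the output, the standard error of its mean is too small, whether or not a residual is added: reported/true about 0.90 to 0.93 at 10% missing and 0.79 to 0.86 at 20%, combining formula and simulation. The same lack of allowance carries over to an output derived from filled values, though its ratio was not calculated. The figures assume the missing rates, R² of 0.05 to 0.30, values missing completely at random and no clustering; the understatement is smaller once between-VDC variation is counted.

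It would be too strong to say that the 95% level fails for every analysis that touches an imputed number, or that the four-visit rate is biased by a known amount. The primary comparison is not reached by this rule, covariate use is probably a small matter, and the four-visit shift is a conditional risk of unknown sign and size. This is a choice worth correcting, not a threat to the main result.

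**What to change.** Replace the sentence on numerical variables with:

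> Outputs are analysed as observed and are not filled by single regression imputation. Missing numerical covariates, and outputs in a sensitivity analysis, are handled by multiple imputation with residual variation, with arm and the cluster structure in the model. Threshold indicators are derived within each imputed set, and results are combined by Rubin's rules.

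This settles the reading of the present sentence, lets the intervals reflect the missing information, and removes the threshold problem however antenatal visits are stored. It needs no new data. The cost is a little more analysis work and slightly wider confidence intervals where imputed values are used.

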### Ethical considerations

The research got the approval from Nepal Health Research Council in 2011. The informed consent forms have been developed according to the WHO and National Ethical Guidelines. Sharing meeting was organized with the district level stakeholders, management committees and mothers groups in all study clusters before randomization and shared about the research objectives, approaches and duration. We also presented findings of our baseline in graphical and pictorial presentation for ease of understanding. The committees and groups were explained by the research team that interventions will be implemented only in half of the VDCs which will be selected randomly. The committees and groups were explained about the modality of interventions.

The enumerators during the end line survey will approach participants in their homes; will take written consent before the interview. Participation of women is voluntary. Also, NPHF has made provision to make study areas safe for field coordinators and enumerators.

### Benefits to control areas

There is no direct benefit to the control VDCs. However, if the trial found to be effective, the government of Nepal has committed to scale up the intervention package starting from the control VDCs.

The intervention will not benefit the individual nevertheless it aims to strengthen already functioning health system. The intervention is not being done at the individual level rather than at the system level. These interventions are strengthening the capacity of health system by reinforcing their ongoing tasks or expanding the scope of their activities.

### Sustainability and scalability

In all intervention components, we are directly working with health care system of Nepal which increases the sustainability of our approach.We trainedfemale community health volunteers, oriented health facility committee members, local youths to actively communicate the importance of skill attendant at birth, manage transportation system in obstetric emergency, mobilize funds and improve security to SBAs and friendliness of health institutions. Every orientation in health facility was participated by community leaders, political representatives, and health personnel and women group members. An existing health system is being strengthening without adding intervention that is not feasible and acceptable. It is hoped that after the end of this intervention the communities will be self-reliant in their capacity to provide skill attendant at childbirth.

### Public engagement

The project encourages public engagement at different levels. Locally members of health facility management committee, female community health volunteers, and local youth groupswere involved starting from formative phase where they identified barriers in utilization of SBA services to design of intervention package.Locally intervention areas will have periodic meeting with community groups, women’s groups, and health facility management committee members. The filed coordinators will be present at each of these meetings every month to help them understand the importance of skill attendant at birth.

In district, regional and national level District Public Health Office (DPHO)/District Health Office (DHO), regional health directorate, district and regional governmental and nongovernmental health agencies were involved. From the very beginning,the researcher was involved in dialogue with district and national level health agencies. The project was approved by the Family Health division (MoHP) and Nepal Health Research Council. It is believed that by involving government agencies in our research workwill increase the utilization of findings of the study.

The findings of the study will be disseminated to policy makers, programme managers of governmental and nongovernmental health organization at district and national levels after completion of the end line survey. We will seek the possibility to lobby policy makers in utilizing key recommendation of our project. For this, findings will be presented to national and international conferences organized by professional bodies like Nepal Pediatric Society (NEPAS), Nepal Society of Obstetricians and Gynecologists (NESOG), Nepal Medical Association and Nepal Public Health Association (NePHA), and Tribhuvan University, Maharajgunj Medical Campus. We will also publish our findings in national and international scientific publications as well as popular papers.

## Discussion

This proposal addresses the issues of achieving MDG 2015 in Nepal. It supports the Safe Delivery Incentive Programme (SDIP) which is central to government’s effort to improve maternal health that aims to increase coverage of skilled birth attendance and also to contribute towards poverty reduction by preventing death and disability [17,18]. The protocol assesses the effectiveness of a package of community based intervention to improve maternal outcome.

The package of intervention includes five components. The first three components address the demand perspective such as increasing family support for pregnant women, making avail the fund to reach the facility and transportation. Similarly, the last two components address the provider perspective at community level such as capacity strengthening of skilled birth attendants in terms of communication training and ensuring security of the service provider.

The intervention package is designed to increase the utilization of skilled birth attendants by overcoming the barriers related to awareness, finance, transport, security etc. If proven effective, the Ministry of Health has committed to scale up the intervention package throughout the country.

## Abbreviations

ANC: Antenatal care; BEOC: Basic emergency obstetric care; DG: Director general; DHO/DPHO: District health office/district public health office; FGD: Focus group discussion; GoN: Government of Nepal; HFMC: Health facility management committee; HV: Health volunteers; IoM: Institute of medicine; IMR: Infant mortality rate; MDG: Millennium development goals; MMR: Maternal mortality rate; NDHS: Nepal demographic and health survey; NHP: National health policy; NHTC: National health training center; NPHF: Nepal public health foundation; PMTCT: Prevention of mother to child transmission; SBA: Skill birth attendant; SDIP: Safe delivery incentive package; SLTHP: Second long term health plan; SMNHLTP: Safe motherhood and neonatal health long term health plan; WHO SEARO: World health office South East Asia regional office.
